### **3.7 Study Duration and Timeline**

1st October 2024- 31st December 2026

Proposal preparation: 1 month

Web-based educational module development: 3 months

Application of ethical approval: 3-6 months

Data collection: 12 months

Data analysis: 5 months  
Write-up and publication: 3 months

The participation duration for each participant is 2 months

### **3.8 Study Visits and Procedures**

- **Visit 1: Pre-Data Collection**
  - Observe clinic workflow to plan and facilitate patient recruitment.
  - Administer pre-intervention survey and address any logistical or procedural issues.
- **Visit 2: Recruitment and Intervention Assignment**
  - Recruit participants and assign them to either the intervention (InTroDuce-Programme) or standard care arms.
- **Visit 3: Follow-Up Assessment**
  - Conduct assessments 1 month post intervention to evaluate post-intervention knowledge, attitudes, and vaccination intention

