## **3.0 Methodology**

### **3.1 Study Type and Design**

This randomised controlled trial (RCT) will be conducted in four primary care clinics in Hulu Langat district which are Klinik Kesihatan Kajang, Klinik Kesihatan Bangi, Klinik Kesihatan Batu 9 and Klinik Kesihatan Balakong. The study duration is 12 months, with recruitment over 6 months. A second follow-up will be conducted one month after providing the InTroDuce-Programme. Two clinics will be randomly assigned to administer the InTroDuce-Programme, while the other two will be provided with standard care, in order to minimise contamination.

(Appendix A: consort diagram)

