## Random Allocation of Clinics

- **Random Assignment:** One clinic from each category (urban and suburban) will be randomly assigned to either the intervention or control group using an online random number generator. This method ensures unbiased allocation and maintains the balance of geographic representation in both groups.
  - **Intervention Clinic:** The clinics will receive the **InTroDuce Programme**, where pregnant women attending the clinic will undergo the educational module on influenza and Tdap vaccination.
  - **Control Clinic:** The clinics will serve as the control group, where pregnant women will receive the standard antenatal care.

**The rationale for Randomization is to minimise contamination.** Randomizing at the clinic level (cluster randomization) rather than at the individual level will help reduce the risk of contamination, where participants in the same clinic may share information or influence each other's behaviour. By assigning entire clinics to either intervention or control, the study ensures that participants within each clinic receive consistent and isolated exposure to the educational materials or standard care.

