## **Phase 3: Implementation and Effectiveness Measurement**

The final phase involves the intervention implementation and evaluating its effectiveness through a randomised control trial (RCT):

1. **Study Design:** A cluster RCT will be used to compare the effectiveness of the **InTroDuce-Programme** (intervention group) versus standard care (control group) in improving the future vaccine uptake.
2. **Outcome Measurement:**
3. The module's effectiveness will be assessed using pre- and post-intervention questionnaires:
  1. **Primary Outcome:** Improvement in participants' knowledge of vaccination safety, benefits, and future uptake intentions.
  2. **Secondary Outcomes:** Identification of barriers to vaccination uptake and socio-demographic factors influencing outcomes.

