### **3.13 Informed Consent/Assent Process**

Patients shall be informed of the study during their usual clinic visits. If they are willing to participate, the consent forms will be signed and dated. If they need to, they are allowed to take the information sheet home to consult with their family members, and another day for getting consent arranged.

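### Section 3.8 surveys women before they are recruited and then has staff assign them to arms, which conflicts with clinic randomisation and leaves the trial baseline misplaced or undefined

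*Protocol*

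**What the plan says.** Section 3.8 of the Protocol lists three visits. The first is headed "Visit 1: Pre-Data Collection" and includes the task "Administer pre-intervention survey and address any logistical or procedural issues". The second covers recruitment: "Recruit participants and assign them to either the intervention (InTroDuce-Programme) or standard care arms". The third is the assessment one month after the intervention.

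Section 3.1 describes a different unit of assignment. It states that "Two clinics will be randomly assigned to administer the InTroDuce-Programme", and its subsection on random allocation explains the reason for "Randomizing at the clinic level (cluster randomization) rather than at the individual level": to limit contamination. The same subsection continues "By assigning entire clinics to either intervention or control".

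On measurement, Phase 3 in section 3.5 says "The module's effectiveness will be assessed using pre- and post-intervention questionnaires". Section 3.6 repeats the pre/post plan, and section 3.9 names a paired t-test among the methods for the knowledge score.

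On consent, section 3.12 requires it in writing, and section 3.13 says "Patients shall be informed of the study during their usual clinic visits". Neither section places consent before or after Visit 1.

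**The concern.** Two instructions in the visit plan do not fit the design.

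First, the survey comes before recruitment. A pre/post comparison needs a score from each enrolled woman, linked to her later score and taken before she sees the module. If the only pre-intervention survey precedes recruitment, its respondents need not be the women who later enrol, and it is unclear whether they have consented to the trial.

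Second, the wording on assignment has staff placing recruited women in one arm or the other. In a trial that allocates clinics there is nothing left to assign once a woman is recruited. Staff who followed the sentence literally would put both arms inside one clinic, with no allocation sequence or concealment described. That is the contamination that clinic allocation is meant to prevent.

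Behind both lies a question that section 3.8 should settle: does a woman, or the person inviting her, know the clinic's arm when she decides whether to join? The outcomes are questionnaire measures of knowledge and vaccination intention. If women already favourable to vaccination enrol more readily in programme clinics, the outcome shifts in the same direction as a real programme effect.

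**Working it through.** This is mainly a comparison of passages. The only arithmetic concerns timing.

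**1. The plan's own figure.** Section 3.4 starts from 216 women, applies a design effect of 1.3 and allows for 20% non-response: 216 × 1.3 = 280.8, and 280.8 / (1 − 0.20) = 351. The stated total is reproduced, and nothing in this point changes it. The design effect also fits allocation by clinic, which is a further sign that section 3.8 is the passage out of line.

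**2. Unit of assignment.**
- Section 3.1: two clinics to the programme and two to standard care, one urban and one suburban in each arm; individual randomisation expressly set aside.
- Section 3.5, Phase 3: a cluster trial.
- Section 3.8, Visit 2: participants are recruited and then assigned.

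The first two agree and the third does not.

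**3. Where the baseline is collected.** There are two ways to read the Visit 1 survey.
- *It is the trial baseline.* It then precedes recruitment, so its link to enrolled women and its consent status are not defined.
- *It is the needs-assessment survey of Phase 1 (section 3.5).* It then serves module development, and section 3.8 contains no trial baseline, because Visit 2 lists only recruitment and assignment and Visit 3 is the follow-up. This reading also fits poorly: Phase 1 comes before the module is developed, whereas Visit 1 is described as preparing for recruitment.

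On either reading section 3.8 does not supply the linked pre-score that sections 3.5, 3.6 and 3.9 rely on.

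**4. Whether the arm is likely to be known at recruitment.** The protocol does not say when clinics are randomised. Its timings bear on the question:
- recruitment period: 6 months (section 3.1);
- follow-up: 1 month after the programme (sections 3.1, 3.6 and 3.8);
- participation per woman: 2 months (section 3.7);
- latest entry at 32 weeks of gestation, with follow-up at 36 weeks (section 3.2).

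Suppose that a woman's 2 months start at recruitment. Her follow-up then falls by month 2, so the module is given by month 2 − 1 = 1 at the latest. For a woman entering at 32 weeks, 36 − 32 = 4 weeks remain, so the module has to be given more or less at entry. If the first woman joins a programme clinic when recruitment opens, that clinic's arm is in use within about one month, and about 6 − 1 = 5 of the 6 recruitment months follow. With even recruitment, that is 5/6, or about 83%, of women.

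This shows that most recruitment would probably take place in clinics whose arm is already operating. It does not measure selective enrolment or bias. The protocol gives no figures on consent by arm or on how attitudes differ between women who join and women who decline.

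**The case against.** The strongest reply is that section 3.8 is loosely worded and the rest of the protocol is clear. Visit 1 reads as set-up by the research team: its other tasks are observing clinic workflow and sorting out logistics. A pre-intervention questionnaire is planned in sections 3.5 and 3.6, and written consent is required in section 3.12. Every other description of allocation is by clinic, and no procedure for randomising individuals appears anywhere. The CONSORT diagram and the consent material were not available for this review and may show the order of steps.

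Much of this stands, and it limits what can be claimed. A reader might make four stronger inferences:

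- *The baseline is invalid.* The text does not show this. It shows a baseline that is misplaced or undefined in the visit plan.
- *Staff will allocate individuals.* The assignment wording is probably loose for an arm that follows from the clinic. The contradiction is real, but the intention elsewhere is clear.
- *The protocol recruits women with the arm known.* It does not say so. Read literally, the Visit 2 sentence even puts assignment after recruitment. Knowledge of the arm is a likely consequence of open clinic allocation and the timings, not a stated procedure.
- *The small number of clinics makes this bias worse.* Selective enrolment driven by knowledge of the arm is systematic, so more clinics would not average it out either.

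What the reply does not remove is that section 3.8 is the operational text staff will follow, and that neither reading of Visit 1 yields a defined trial baseline. Visit order and unit of assignment belong in the protocol, so a separate analysis plan would not settle them.

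**Conclusion.** The point holds as an internal contradiction with a practical consequence. Section 3.8 conflicts with section 3.1 on the unit of assignment, and it leaves the per-woman baseline misplaced or undefined although the pre/post comparison depends on it. Followed literally, it would give an unlinked pre-score, or both arms within one clinic.

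Selective enrolment is a risk and not a stated feature of the plan. It rests on three things: allocation is by clinic, no blinding of recruiters or women is described, and the timings put the module into use early in a six-month recruitment period. The timing step assumes that participation runs from recruitment and that programme clinics recruit from the start. The direction of concern is an apparent programme effect. Its size cannot be derived from the documents, and any figure would only restate the assumption put in. Because such bias cannot reliably be repaired after enrolment, the text should be corrected even though part of the problem is probably wording.

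**What to change.** Rewrite section 3.8 so that it agrees with section 3.1:

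- **Visit 1:** clinic set-up only. If a Phase 1 survey is meant, move it to section 3.5 and label it as such.
- **Visit 2, in this order:** invite consecutive eligible women with the same information sheet in all four clinics; take written consent; give the baseline questionnaire; only then disclose the clinic's arm and, in programme clinics, give the module.
- **Assignment:** replace the instruction to assign participants with a statement that each woman's arm is that of her clinic.
- **Timing:** state when clinics are randomised relative to the start of recruitment.
- **Screening log:** record by clinic the numbers approached, eligible and consenting, so that selective enrolment can be seen.
- **Analysis:** adjust the between-arm comparison for baseline score. The detail can sit in the analysis plan, but the baseline has to be collected as above for this to be possible.

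The cost is protocol and information-sheet wording, a small logging burden for staff in four clinics, and ethics committee review of the common sheet. That sheet can describe both arms and so still meet the promise in section 3.12 to explain procedures before consent. The sample size does not change and no visit is added.

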### **3.9 Statistical Analysis Plan**

#### **Statistical Methods:**

- a. Primary outcome (knowledge score) will be analyzed using paired t-tests or Mann-Whitney U tests for non-parametric data.
- b. Secondary outcomes (vaccination uptake which is yes or no) will be analyzed using multiple logistic regression to determine the factors associated with no vaccination uptake intention.

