### **Specific objectives:**

- 1) To determine the sociodemographic factors and clinical variables among study population.
- 2) To determine the prevalence of future vaccination uptake following the InTroDuce-Programme.
- 3) To evaluate the level of participants' attitudes and barriers towards future vaccination uptake before and after the InTroDuce-Programme.
- 4) To determine the effectiveness of the InTroDuce-Programme in improving knowledge and future uptake of influenza and Tdap vaccination among pregnant mothers.
- 5) To determine the factors associated with low future uptake of vaccine with socio-demographic factors (age, race, income, education) among pregnant mothers.

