### **3.6 Data Collection**

- **Knowledge and attitude Assessment:** A pre- and post-intervention questionnaire will assess knowledge about the importance, safety, and benefits of vaccination (vaccine literacy)

- **Vaccination future uptake:** Intention of future vaccine uptake of the influenza and Tdap vaccines will be assessed using questionnaire
- **Follow-up:** Participants will be followed up at one month after providing intervention to assess intention of future vaccine uptake and barriers if not intending for vaccination uptake

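### The primary knowledge analysis names a within-woman paired t-test with an independent-groups fallback, and fixes no clear comparison of intervention with control

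*Protocol*

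**What the plan says.** The protocol's section 3.9 has two items. Item (a) covers the knowledge score: "Primary outcome (knowledge score) will be analyzed using paired t-tests or Mann-Whitney U tests for non-parametric data". It names no groups and no time points. Item (b) covers uptake intention as a yes/no outcome and plans "multiple logistic regression to determine the factors associated with no vaccination uptake intention". It does not name treatment arm as a term.

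The rest of the protocol describes a two-arm comparison. Specific objective 4 is "To determine the effectiveness of the InTroDuce-Programme in improving knowledge and future uptake of influenza and Tdap vaccination among pregnant mothers". Section 3.1 says "Two clinics will be randomly assigned to administer the InTroDuce-Programme, while the other two will be provided with standard care". Section 3.5, Phase 3, calls the study a cluster RCT of the programme against standard care and gives the primary outcome as "Improvement in participants' knowledge of vaccination safety, benefits, and future uptake intentions". On measurement, section 3.6 says "A pre- and post-intervention questionnaire will assess knowledge about the importance, safety, and benefits of vaccination", and section 3.8 places the follow-up assessment one month after the intervention.

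**The concern.** A paired t-test needs matched observations. No woman in an intervention clinic is matched to a woman in a control clinic, so the only available pairing is the two questionnaires of one woman. The test then asks whether scores rose, not whether they rose more with the programme than without it.

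Scores can rise for other reasons. A woman who has seen the questions once may do better the second time, and antenatal care continues between the two questionnaires. A significant paired test among intervention women could be reported as effectiveness when control women improved just as much.

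The fallback adds a second problem. The rank counterpart of the paired t-test is the Wilcoxon signed-rank test. Mann-Whitney U is for two independent groups. If it were applied to intervention versus control, the trial would compare arms only when the data look non-normal. If it were applied to before versus after, it would ignore the pairing and still not compare arms.

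**Working it through.** **What each named test can compare**

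| Test in 3.9(a) | Data it needs | Contrast available here | Uses control clinics as comparator? |
|---|---|---|---|
| Paired t-test | Matched pairs | After minus before, same woman | No |
| Mann-Whitney U, between arms | Two independent groups | Intervention versus control | Yes, but only as the fallback |
| Mann-Whitney U, before/after | Two independent groups (violated) | After versus before | No |

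**The protocol's own sample size (section 3.4).** Inputs are 55% versus 36%, two-sided 5%, 80% power, design effect 1.3 and 20% non-response.

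- The Fleiss formula gives 107 per arm (protocol: 108). Power at 108 per arm is 80.5%.
- 216 × 1.3 = 280.8, taken as 281.
- 281 / 0.80 = 351.25, against 351 stated.

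The figure reproduces. It is a comparison of proportions between two arms, so the trial was sized on a contrast that a paired t-test does not make.

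**Illustration of the paired test.** The protocol gives no SD, correlation or expected retest gain for the knowledge score, so these inputs are assumptions:

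- n = 140 completers per arm (281 / 2 = 140.5);
- programme effect zero;
- the same true gain g in both arms, in SDs of the change score.

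The paired t statistic has 139 degrees of freedom and noncentrality g × √140. The two-sided 5% critical value is 1.977.

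| g | g × √140 | P(paired test significant, intervention arm) | P(significant in intervention, not in control) |
|---|---|---|---|
| 0.1 | 1.18 | 0.22 | 0.22 × 0.78 = 0.17 |
| 0.2 | 2.37 | 0.65 | 0.65 × 0.35 = 0.23 |
| 0.3 | 3.55 | 0.94 | 0.94 × 0.06 = 0.06 (0.055 unrounded) |

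A separate simulation (3,000 runs, raw SD 1, before/after correlation 0.5, so the change-score SD is √(2 × (1 − 0.5)) = 1) gave 0.22, 0.66 and 0.95 for the paired test. In the same runs a between-arm t-test on change scores rejected 4.6% to 5.1% of the time. The last column of the table shows that testing each arm separately and contrasting the two p-values does not repair the plan.

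**Why the replacement must also account for clinic.** That 5% holds only without a clinic effect. With four clinics of 70 women and no programme effect, an arm comparison that ignores clinic rejected 8.5%, 13% and 35% of the time at assumed intraclass correlations of 0.004, 0.01 and 0.05. The design effect of 1.3 itself implies about 0.3 / (70.25 − 1) = 0.0043 at 281 women, or 0.3 / (87.75 − 1) = 0.0035 at 351.

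**What four clinics allow.** A clinic-level model with intercept, arm and stratum leaves 4 − 3 = 1 degree of freedom, with a two-sided 5% critical value of 12.7. One clinic per stratum goes to each arm (section 3.1, random allocation of clinics), so there are 2 × 2 = 4 possible allocations. An exact randomisation p-value cannot fall below 1/4.

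**The case against.** A reader might infer that the sponsor has decided to ignore the control arm. The text does not go that far. Item (a) names neither groups nor time points, and the protocol describes two arms throughout. The two tests may be a garbled version of a sensible plan, with the paired test within arms and Mann-Whitney between them. That stands as a limit on the claim: the fault is a mismatched test and an unclear contrast, not a stated choice to drop the controls.

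A reader might also infer that both named tests compare before with after. That is wrong. Mann-Whitney U is the one named test that could compare the arms.

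The Phase 3 sentence on comparing the arms is about vaccine uptake, not knowledge. That is correct, and objective 4 is the better anchor because it names knowledge explicitly.

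The percentages rest on assumed gains. They show how the test behaves and are not this trial's error rate.

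A separate analysis plan may exist. That does not answer the point. The protocol does not leave the primary test open: it names one that does not fit the aim, and a later between-arm analysis would depart from it.

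**Conclusion.** The point holds in this form: the paired t-test in 3.9(a) tests change within women, its named fallback is not its rank counterpart, and no between-arm comparison of knowledge is clearly fixed. Item (b) does not fill the gap, because it concerns intention and looks for associated factors. As written, the primary analysis cannot answer objective 4 for knowledge.

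The size depends on how much scores would rise without the programme. If they would not rise at all, the paired test keeps its 5% error. At modest common gains of 0.1 to 0.3 SD of the change score, it would suggest a benefit that does not exist in about 22% to 94% of trials. This assumes 140 completers per arm, no clinic effect, and that control women complete both questionnaires, which sections 3.6 and 3.8 imply without saying so. The mismatch between test and question does not depend on any of these numbers.

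**What to change.** Replace 3.9(a) with wording such as: *The one-month knowledge score will be compared between intervention and control, adjusting for the same woman's baseline score and for urban/suburban stratum, with a stated method that accounts for clinic. The primary result is the adjusted mean difference, intervention minus control, with its 95% confidence interval. Changes within each arm are descriptive only.* For skewed scores, name a rank-based comparison between arms, so that the contrast stays the same whatever the data look like. Do not rely on a bootstrap over four clinics.

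State plainly that four clinics leave about 1 degree of freedom for a clinic-level test, so the interval will be wide and the conclusion limited. Rewording alone does not remove that limit.

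The Phase 3 primary outcome also includes uptake intention. This change settles only the knowledge part, and the protocol should say how intention is compared between arms.

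The cost is a less certain, and possibly less favourable, primary result than the paired test would give. No new data are needed, provided the pre-intervention questionnaire is linked to the women later enrolled. Section 3.8 puts that survey at Visit 1 and recruitment at Visit 2, so the link should be confirmed.

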### 3.4 Sample Size

The sample size was calculated using openEpi software based on earlier study which demonstrated proportion of 55% in intervention group (website with vaccine information) and 36% in control group (usual care) (14) The final sample size is 351 based on the design effect of 1.3, 20% of non-response rate, 95% CI, 80% of power and significant value of 0.05.

| Examples                                 | Sample Size: X-Sectional, Cohort, & Randomized Clinical Trials |        |                |
|------------------------------------------|---------------------------------------------------------------------------|--------|----------------|
| Help                                     |                                                                           |        |                |
| Two-sided significance level(1-alpha):   |                                                                           |        | 95             |
| Power(1-beta, % chance of detecting):    |                                                                           |        | 80             |
| Ratio of sample size, Unexposed/Exposed: |                                                                           |        | 1              |
| Percent of Unexposed with Outcome:       |                                                                           |        | 36             |
| Percent of Exposed with Outcome:         |                                                                           |        | 55             |
| Odds Ratio:                              |                                                                           |        | 2.2            |
| Risk/Prevalence Ratio:                   |                                                                           |        | 1.5            |
| Risk/Prevalence difference:              |                                                                           |        | 19             |
|                                          | Kelsey                                                                    | Fleiss | Fleiss with CC |
| Sample Size - Exposed                    | 109                                                                       | 108    | 118            |
| Sample Size-Nonexposed                   | 109                                                                       | 108    | 118            |

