| Total sample size:                       | 218                                                                       | 216    | 236            |

Design effect= 1.3

216x 1.3=281

Taking into consideration non-respondent rate of 20%, final sample size is 351.

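### Clinics are randomised and the sample size carries a design effect of 1.3, but the methods named in section 3.9 ignore clinic, so a between-arm comparison made with them does not hold its 5% error rate

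*Protocol*

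**What the plan says.** Section 3.1 allocates whole clinics: "Two clinics will be randomly assigned to administer the InTroDuce-Programme, while the other two will be provided with standard care". Under Random Allocation of Clinics the allocation is stratified, "One clinic from each category (urban and suburban) will be randomly assigned to either the intervention or control group", and the unit is explicit: "Randomizing at the clinic level (cluster randomization) rather than at the individual level". Phase 3 in section 3.5 repeats the label: "A cluster RCT will be used to compare the effectiveness".

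Section 3.4 starts from 216 women and applies "Design effect= 1.3", which gives 281, then allows for 20% non-response to reach 351. It gives no intracluster correlation (ICC).

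Section 3.9 is the only analysis text in the protocol. The knowledge score "will be analyzed using paired t-tests or Mann-Whitney U tests". Yes/no uptake intention goes into a multiple logistic regression whose stated purpose is to find factors associated with not intending vaccination. No random effect, clinic-level comparison or clustered standard error is mentioned.

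**The concern.** A design effect above 1 states that women in the same clinic resemble each other. The methods in section 3.9, as named, treat women as independent. The analysis therefore contradicts both the allocation and the sample-size assumption.

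The design effect in section 3.4 does not repair this. It adds women to protect power. It does nothing to the standard error of a test that leaves clinic out. When the tested factor is constant within clinic, as arm is here, that standard error is too small, the confidence interval too narrow and the p-value too low. With only two clinics per arm, an ordinary difference between clinics could be reported as an effect of the programme.

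**Working it through.** **Inputs.** From the protocol: four clinics, two per arm, one urban and one suburban in each (section 3.1); 55% against 36%, two-sided 5%, 80% power, design effect 1.3, 20% non-response (section 3.4). Not in the protocol: the ICC, and the share of between-clinic variance that lies between urban and suburban clinics. Both are shown as ranges.

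**Reproducing the sample size.** The two-proportion formula without continuity correction gives 107 per arm; the protocol's software output shows 108. Then 2 × 108 = 216, 216 × 1.3 = 280.8, and 280.8 / 0.8 = 351. The stated total reproduces.

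**ICC implied by the design effect.** With 281 women analysed, m = 281 / 4 = 70.25 per clinic. From DE = 1 + (m − 1) × ICC, ICC = 0.3 / 69.25 = 0.0043.

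**Type I error of a between-arm test that ignores clinic.** If a share s of the between-clinic variance is urban/suburban, that part cancels from the arm difference, because each arm has one clinic of each kind. The effective inflation is then

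DE = 1 + (m(1 − s) − 1) × ICC,

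and the true two-sided error of a nominal 5% test is 2 × (1 − Φ(1.96 / √DE)).

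| ICC | DE, s = 0 | Error, s = 0 | DE, s = 0.5 | Error, s = 0.5 |
|---|---|---|---|---|
| 0.0043 (from DE 1.3) | 1.30 | 8.6% | 1.15 | 6.7% |
| 0.01 (assumed) | 1.69 | 13% | 1.34 | 9% |
| 0.02 (assumed) | 2.38 | 20% | 1.68 | 13% |
| 0.05 (assumed) | 4.46 | 35% | 2.71 | 23% |

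Simulation with four clinics of 70 women and s = 0 gave 8.4%, 12.9%, 21.3% and 35.8% for an independent-samples t-test, and 8.5%, 12.3%, 20.9% and 34.8% for Mann-Whitney. Simulation with s = 0.5 gave about 6.8%, 9%, 13% and 24% for the t-test.

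**Clinic-level test.** A t-test on clinic means with 2 df stays near 5% when s = 0. With s = 0.5 it is conservative, at about 3.3% to 4.5%. The 1-df test that fits the stratum stays near 5% in both cases.

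**Power of the clinic-level test.** With 281 / 2 = 140.5 women per arm and DE 1.3:

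- SE = √(1.3 × (0.36 × 0.64 + 0.55 × 0.45) / 140.5) = √(1.3 × 0.4779 / 140.5) = 0.0665.
- Non-centrality = 0.19 / 0.0665 = 2.86.
- Normal reference, as section 3.4 implicitly uses: power about 80%.
- t on 2 df, critical value 4.30: power about 36%.
- t on 1 df, critical value 12.71: power about 18%.

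**The case against.** A reader might infer that every method in section 3.9 has an inflated false-positive rate of the size tabulated. The protocol does not support that.

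- The paired t-test compares before with after within a woman. It makes no comparison between arms, so the table does not apply to it. Its fault is different: it cannot estimate the programme effect.
- The logistic regression is presented as a search for associated factors, in line with specific objective 5 (age, race, income, education). Those factors vary within clinic, so the inflation for a factor constant within clinic does not carry over to them. It applies only if an arm term is added and tested.

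The stratified allocation also matters. The s = 0 figures are the upper case, and the excess would vanish if all between-clinic variance were urban/suburban. The protocol gives no reason to assume that.

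Only the 8.6% starts from the protocol's own number. Section 3.4 applies the 1.3 to a proportion, so using it for the knowledge score is a further assumption.

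Finally, one could say that such detail belongs in a separate analysis plan. That would answer silence. Here section 3.9 names specific methods, and they conflict with the stated design.

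These points narrow the scope and size. The contradiction between design and analysis remains.

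**Conclusion.** The point stands for between-arm comparisons and should be corrected before analysis. At the design effect the protocol itself assumes, a nominal 5% test that ignores clinic has a true error of about 8.6% with no urban/suburban share of the between-clinic variance, and about 6.7% with a half share. Over assumed ICCs of 0.01 to 0.05 the range is about 13% to 35%, or about 9% to 23% with the half share. The higher ICCs and the half share are assumptions; the protocol states neither.

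The 80% power in section 3.4 is also not the power of a valid analysis with four clinics. Under the same design effect it is about 36% on 2 df or 18% on 1 df. Those figures are for a proportion without baseline adjustment, which could improve precision.

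**What to change.** State in section 3.9 that the programme effect is a between-arm comparison with inference at clinic level, and name the analysis:

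1. Stage 1: regress each woman's one-month outcome on her baseline value, without arm (linear for the knowledge score, logistic for yes/no intention).
2. Stage 2: summarise the residuals by clinic and compare arms with a t-test on 2 df, or 1 df if the urban/suburban stratum is fitted. Choose in advance; the 2-df test is conservative if the strata differ.

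For the knowledge score, a linear mixed model with a clinic random effect and Kenward-Roger degrees of freedom is an alternative. That correction does not carry over directly to the yes/no outcome. Uncorrected sandwich-error GEE should not be relied on with four clusters. The paired t-test may describe change within an arm but should not be presented as the test of the programme.

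Restate the power in section 3.4 for the chosen analysis and give the ICC assumed. The text change is small; the statistical cost is not. Intervals widen, and unless the design changes the trial would probably miss the effect it was sized for. The sponsor should know this when deciding.
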